### Sample size estimation

2.4

The sample size was calculated to provide adequate power to examine associations between genetic polymorphisms and severity of endocrine symptoms associated with tamoxifen treatment, as well as adherence with tamoxifen treatment. In general, a larger sample size for an association analysis allows for the detection of a smaller effect size at a specific statistical power and level of significance. However, a small effect size may not be of clinical importance. In consideration of both clinical relevance and statistical power, we aim to detect a reasonable effect size of *R*^2^ = 0.05 for a genetic predictor of severity of endocrine symptoms of tamoxifen treatment as well as for an association between the severity of endocrine symptoms and level of adherence with tamoxifen treatment.

Using PASS 13 (NCSS, Kaysville, UT), it is estimated that a sample size of 152 patients would give our study 80% power at a 5% level of significance to detect an effect size of *R*^2^ = 0.05 (ie, if a specific polymorphism explains at least 5% of the variance in the severity of symptoms of tamoxifen treatment or if the severity of symptoms explains 5% of variance in adherence to the treatment, they will be detectable with 80% power at 5% significance level).

Since our follow-up measurements are based on brief telephone interviews, we anticipate that the nonresponse rate will be relatively low. In fact, all of the patients completed the 3-month follow-up in our ongoing pilot study. Furthermore, on the basis of a 1-year crude death rate of breast cancer patients in Hong Kong (4.4%) (WHO, http://survcan.iarc.fr/index.php) and assuming an average non-response rate for our follow-up questionnaires of <3% for every 3 months, we anticipate that the overall attrition rate in our 18-month prospective cohort study will be 24%. Therefore, we will recruit 200 eligible patients into the study.

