### Genomic assessment

2.6

At enrolment, saliva samples will be collected from patients and stored in a −80°C freezer. Total genomic DNA will be extracted from the saliva using QIAamp DNA Mini Kit (Qiagen, USA) as per supplier's instructions. Genotype analyses will be carried out with ready-to-order TaqMan assays from Thermo Fisher. All patients will be tested for allelic variations in 2 cytochrome P450 enzyme genes (ie, UDP glucuronosyl transferase and sulfotransferase) and 14 drug transporter genes (ie, CYP3A4, CYP3A5, CYP2C9, CYP2C19, CYP2D6, CYP1A2, CYP2B6, UGT1A4, UGT2B7, UGT1A8, UGT2B15, ABCC1, ABCB1, ABCC2). These SNPs were selected because they were reported to be involved in tamoxifen metabolism, which may affect the occurrence and severity of endocrine symptoms.^[20,22]^

Based on the available genotype data, CYP2D6 alleles (as an example) will be assigned a value that reflects the expected activity of the CYP2D6 enzyme for which they code. For example, fully functional CYP2D6 alleles (eg, ∗1, ∗2, ∗33, ∗35) will be assigned a score of 1. CYP2D6 alleles associated with reduced enzyme activity (eg, ∗9,∗10, ∗17, ∗29, ∗37, ∗41, ∗45, ∗46) will be scored as 0.5. The null CYP2D6 alleles (eg, ∗3-∗8, ∗11-∗16, ∗18-∗20, ∗38, ∗40, ∗42, ∗44, ∗56) and their duplications will receive a value of 0. Duplications of fully active alleles (eg, ∗1×N, ∗2 × N, ∗35 × N) will be assigned a value +1, rendering a score of 2 for each of these duplicated variants. Duplicated reduced activity alleles (eg, ∗41 × N and ∗45 × N) will be assigned a value of +0.5, yielding a score of 1.^[35]^

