The genetic factors will be examined as individual SNPs and haplotypes of SNPs from different candidate loci, as appropriate. The distribution of genotypes in candidate SNPs will be tested for Hardy–Weinberg equilibrium (HWE) using Fisher exact test. SNPs in conformation with HWE will be used in regressions analyses to determine their relative contribution to the overall severity of the symptoms associated with tamoxifen treatment with adjustment for potential confounders, including age, menopausal status, stage of cancer at diagnosis, and treatment received. The linkage disequilibrium between SNPs in candidate loci will be analyzed using Haploview (Daly Lab, Cambridge, MA) and haplotypes will be created. The relationships between these haplotypes and overall severity of the symptoms of tamoxifen will be analyzed by the regression-based approach of Zaykin et al^[36]^ after adjusting for potential confounders with the use of a permutation test. Statistical significance will be evaluated using permutations with 10,000 replications. Inflated overall type I error rate will be controlled using the approach of Benjamini and Hochberg.^[37]^ Furthermore, multivariable regression analysis will examine the associations between overall adherence with tamoxifen treatment and overall severity of the symptoms of tamoxifen treatment with adjustment for the above potential confounders. All statistical analyses unless otherwise specified will be performed using SAS release 9.4 (SAS Institute, Cary, NC). All statistical tests will be 2-sided and a *P* value <.05 will be considered statistically significant.

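### Read as written, the Hardy–Weinberg test at P < .05 automatically excludes SNPs from the regressions, so correctly genotyped candidate SNPs can be lost by chance

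*Protocol article*

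**What the plan says.** Section 2.7 sets out the sequence. First, "The distribution of genotypes in candidate SNPs will be tested for Hardy–Weinberg equilibrium (HWE) using Fisher exact test". Next comes the entry rule: "SNPs in conformation with HWE will be used in regressions analyses to determine their relative contribution". The section closes with a rule for all tests: "All statistical tests will be 2-sided and a *P* value <.05 will be considered statistically significant". It also says "Inflated overall type I error rate will be controlled using the approach of Benjamini and Hochberg", without naming the family of tests covered. It does not describe what happens to a SNP that fails.

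Section 2.6 (Genomic assessment) says that the SNPs were chosen for a reported role in tamoxifen metabolism. It counts two genes "and 14 drug transporter genes" and gives no number of SNPs. TaqMan assays are the only platform named. For CYP2D6 it defines an activity score that covers null alleles, reduced-function alleles and duplications ("Duplications of fully active alleles" have their own value).

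**The concern.** The HWE rule is something the article fixes, not a detail it leaves open: conformity decides whether a SNP is analysed. HWE describes genotype proportions in a population. A departure can reveal faulty genotype calls, which is why it is checked. A regression of symptom severity on genotype in a cohort remains valid without it. One P value just under .05, among many such tests, is weak evidence of a fault, yet under this rule it removes the SNP.

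Each SNP was selected in advance for a reported function, so each one lost is a planned hypothesis that goes untested. CYP2D6 deserves particular attention because section 2.6 expects copy-number variation there. A patient with only one gene copy can look homozygous on a SNP assay, and the resulting shortage of heterozygotes is what an HWE test detects.

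**Working it through.** **The plan's own figures.** Section 2.4 gives 152 evaluable patients for R² = 0.05, 80% power and two-sided 5%. With f² = 0.05/0.95 and noncentrality N × f², the one-predictor F test has power 0.802 at N = 152 and 0.7998 at N = 151. Allowing for 24% attrition, 152/(1 − 0.24) = 200. Both figures reproduce, and the HWE rule does not affect them. Saliva is taken at enrolment, so N = 200 is the number genotyped.

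**Inputs**
- Test: exact, per SNP (section 2.7).
- Threshold: two-sided P < .05, inferred from the general rule in section 2.7.
- N = 200 (section 2.4: "Therefore, we will recruit 200 eligible patients into the study").
- Number of SNPs: not given. Section 2.6 counts 2 + 14 = 16 genes or gene families; one SNP each gives 16 (assumption). I also show 14 and 30.
- Minor allele frequency (MAF): not given; range 0.02 to 0.5.

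**Step 1: false exclusion of one SNP.** Given the allele counts, the exact test uses

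P(n_AB) = N! n_A! n_B! 2^(n_AB) / [n_AA! n_AB! n_BB! (2N)!]

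and its P value sums the outcomes no more probable than the one observed. I averaged the rejection probability under true HWE over the binomial distribution of the allele count, at N = 200:

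| MAF | P < .05 | P < .001 |
|---|---|---|
| 0.02 | 1.1% | 0.02% |
| 0.05 | 2.2% | 0.03% |
| 0.1 | 2.9% | 0.05% |
| 0.2 | 3.8% | 0.06% |
| 0.3 | 4.1% | 0.07% |
| 0.4 | 4.1% | 0.08% |
| 0.5 | 4.7% | 0.07% |

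The exact test is conservative, so the rate stays below the nominal 5%. About 4% is representative for common SNPs.

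**Step 2: loss over the set.** With m independent SNPs at 4% each, the expected loss is 0.04m and the chance of at least one loss is 1 − 0.96^m.
- m = 14: 0.56 lost; 44%.
- m = 16: 0.64 lost; 1 − 0.96^16 = 48%.
- m = 30: 1.2 lost; 1 − 0.96^30 = 71%.

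At P < .001 with 16 SNPs of MAF 0.3, the chance of any loss is 1 − (1 − 0.00073)^16 = 1.2%.

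**Step 3: CYP2D6, conditional on an assumption.** Suppose a deletion allele has frequency d and the assay does not see copy number, so one-copy carriers are called homozygous. Take d = 0.05 and one SNP allele at 0.30, leaving 0.65 for the other. Called heterozygotes are 2 × 0.65 × 0.30 / (1 − 0.05²) = 0.391, against 0.432 expected from the apparent allele frequencies: a deficit of about 9.5%. Simulated exclusion (20,000 replicates, N = 200, SNP allele frequency 0.1 to 0.5):

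| Assumed d | Excluded at P < .05 | Excluded at P < .001 |
|---|---|---|
| 0 | 3–5% | ≤0.1% |
| 2% | 7.5–9% | 0.3% |
| 5% | 24–26% | about 2% |
| 8% | 48–53% | 9–10% |

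Duplications behave differently. If duplicated heterozygotes are called correctly there is no effect. If every one is miscalled, exclusion at P < .05 is about 3–6% at a 1% duplication frequency and 4–27% at 5%.

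**The case against.** **The threshold is inferred.** No cut-off stands beside the HWE test, and an article may leave call review and a stricter limit to a fuller document. If that document sets P < .001, chance loss nearly disappears. This stands as a limit on the conclusion. It does not remove the point, because the article states the entry rule and only one threshold.

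**The Benjamini–Hochberg sentence is just as general.** If it covered the HWE tests and all SNPs were in HWE, the chance of any false exclusion would be about 5% at most. The text ties it to the HWE tests no more than it rules that out, so the ambiguity needs resolving.

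**The harm is limited.** Chance exclusion does not depend on the symptom outcome. It neither biases the retained estimates nor inflates their type I error. That is correct; the cost is lost hypotheses.

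**The CYP2D6 mechanism is a calling problem, which HWE testing exists to catch.** That is fair, and it supports testing and then reviewing the calls. It does not support dropping the SNP without review. The activity score also presupposes some copy-number information, so an assay blind to copy number is not established.

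A reader might infer more: that the study could end up reporting nothing on CYP2D6, or that selecting patients by disease makes real departures likely. The article does not support either. The rule is written for individual SNPs, and neither the activity score nor the haplotype analysis is said to be subject to it. Nothing in the article supports or sizes a disease-selection effect.

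**Conclusion.** The concern holds in a limited form. As the article reads, HWE conformity at P < .05 decides which SNPs are analysed, and this is a poor use of a quality check.

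The size is modest: about 2–5% false exclusion per SNP for MAF 0.05 to 0.5, and roughly an even chance of losing at least one of 16 valid SNPs. This rests on the inferred threshold, an assumed SNP count and independence between SNPs, although the plan itself expects linkage disequilibrium within loci. Using the nominal 5% would give 0.8 expected losses and 56% for 16 SNPs, which overstates the risk because the planned test is exact.

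Extra risk to CYP2D6 SNPs is plausible but conditional. It comes mainly from unrecognised deletions, whose frequency the article does not give, and only slightly from duplications unless heterozygotes are miscalled.

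**What to change.** In section 2.7, replace the entry rule with a flagging rule:
- Test HWE as a genotyping-quality flag at a stated strict threshold, for example P < .001, or .05 divided by the number of SNPs (.05/16 = .0031 for 16).
- For each flagged SNP, review the genotype calls and any copy-number information already available.
- Exclude a SNP only if a genotyping fault is demonstrated. Otherwise analyse it, mark it as flagged, and report a sensitivity analysis without the flagged SNPs.
- State whether the rule also applies to the haplotypes and the CYP2D6 activity score, and whether the Benjamini–Hochberg procedure covers the HWE tests.

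The cost is wording and a little review time, with no change to the sample size. The small downside is that a SNP with a mild genotyping fault may stay in the analysis, marked as flagged.

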## Discussion

3

Adjuvant tamoxifen, an essential treatment for ER+ breast cancer, has been used for >3 decades to reduce the risk of breast cancer recurrence and mortality.^[38]^ To ensure optimal benefits, patients must take tamoxifen for at least 5 years.^[39]^ Despite the acknowledged benefits of both reduced recurrence and increased survival rates, adherence to tamoxifen is less than ideal. Approximately 1 in 5 patients who are prescribed tamoxifen do not achieve the optimal adherence threshold of ≥80% during the first year of treatment, with a subsequent 7% to 10% discontinuation rate per year. By the fourth or fifth year of treatment, the adherence rate is as low as 50%.^[40]^ The most significant factor that contributes to nonadherence is the tamoxifen-related endocrine symptom profile. Symptoms include sudden, severe, and often permanent vasomotor symptoms and related insomnia, somatic symptoms, depression, and sexual dysfunction.^[41]^

Adjuvant endocrine therapy is associated with many adverse effects that can significantly decrease patients’ quality of life and lead to substantial economic loss because of medical expenses and inability of patients to function well in their existing roles in family and in society.^[42]^ Untreated side effects may lead to early discontinuation of treatment and poor adherence, which could compromise overall survival. With >3 million breast cancer survivors and longer survival times with current treatment alternatives, management of survivors’ health issues will increasingly fall to primary care clinicians. The most effective management is a multifactorial approach that addresses patients’ symptoms, health promotion, and referrals.^[42]^

The optimal management strategy for tamoxifen is one that considers the balance between the drug's potential benefits and adverse effects. The way that tamoxifen is metabolized and its potential toxicities are partially influenced by each patient's genetic makeup.^[43]^ The aim of this study is to determine whether, and how, symptoms of tamoxifen correlate with drug adherence and with polymorphisms in genes that regulate the metabolism of tamoxifen in Chinese breast cancer patients. We hypothesize that patients with more severe endocrine symptoms (ie, psychological, somatic, vasomotor, sexual) are less likely to adhere to tamoxifen treatment. In addition, we hypothesize that a relationship exists between the severity of tamoxifen-induced symptoms and allelic variations in tamoxifen metabolism-related genes. To date, studies have focused primarily on the associations between genetic polymorphisms and tamoxifen efficacy^[44,45]^ and not on the association between these factors and tamoxifen-induced symptoms and subsequent adherence. Adherence could be improved by understanding the factors that are associated with patients who are less likely to adhere and any modifiable factors (eg, barriers and facilitators) to their adherence.^[46]^ This increased understanding could contribute to the development of individualized symptom management interventions for patients who are prescribed tamoxifen, ultimately leading to greater adherence and reduced risks of breast cancer recurrence and death.

This study is significant in that it will provide preliminary evidence on the factors associated with tamoxifen adherence in Chinese breast cancer patients. The results of this study may lead to larger descriptive and interventional studies that will evaluate different approaches to increase tamoxifen adherence rates and its clinical efficacy.

It is increasingly recognized that people are prescribed medications that will not help them and could even harm them. The increased recognition that clinicians must account for individual variability in therapeutic effects and symptoms is driving the recent momentum in ’precision’ health care.^[47]^ This more personalized approach is informed by a different type of clinical trial that focuses on individual, not average, responses to therapy and which probes the specific factors that influence patients’ responses to therapy, including genetic and behavioral, among others.^[48]^ In this study, we will consider the relationships between three critical factors (ie, endocrine symptoms of tamoxifen, drug adherence, genetic polymorphisms) that may influence the therapeutic outcomes of adjuvant tamoxifen (eg, disease recurrence, mortality). In the long term, this project is a stepping stone in the further development of personalized adjuvant tamoxifen and tailored symptom management interventions for breast cancer patients based on their individual genomic profile.

This study started in November 2016 and is on-going status at the present time.
